### **3.2. Sample size**

The sample size was calculated using PASS (Power Analysis and Sample Size), version 11 (Number Cruncher Statistical Systems). The calculation was based on detecting a MCID of 7 points on Oswestry Disability Index (ODI), with a standard deviation of 15.1 points derived from a pre-trial study. A statistical power of 90% and a two-sided alpha of 0.05 were assumed. The calculation was based on the primary objective of demonstrating the superiority of the combination therapy over YBT or LOPM alone, using the Dunnett's test for the two primary comparisons. The initial calculation indicated a requirement of 113 participants per group. After accounting for a 15% dropout rate, the sample size was set at 133 participants per group. To ensure robust multi-center recruitment, the target sample size was further increased to 146 participants per group.

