## **6. Observation endpoints and clinical outcomes**

### **6.1. Clinical observation endpoints**

Efficacy measures will be recorded at baseline and 3 days, 1 week, 2 weeks, 6 weeks, 14 weeks, and 26 weeks after randomization. The measurement instruments will be ODI for the functional disability, VAS for the leg and low back pain, and 12-Item Short Form Health Survey (SF-12) for the quality of life. Blood routine tests and liver and kidney function tests will be conducted before randomization and at 2 weeks after randomization. In addition, detailed records of each patient's gastrointestinal discomfort, skin

allergies, and other adverse events will be collected at 2 weeks after randomization to assess safety. At the 26-week post-randomization follow-up, a repeat MRI will be performed. The change in the sagittal area of the disc herniation from baseline to 26 weeks will be measured, with a reduction of  $\geq 40\%$  defined as the occurrence of disc resorption. The disc resorption rates will be calculated. The primary outcome will be change in ODI from baseline to week 2. The minimal clinically important difference (MCID) for ODI will be set at  $\geq 7$  points, consistent with prior studies. Secondary outcomes will include leg and low back pain VAS, SF-12, adverse events, and disc resorption rates.

(1) ODI

ODI assesses the effect of pain on normal daily activity including the ability to and intensity of lifting, care for oneself, walk, sit, sexual function, stand, social life, sleep and travel, ranging from 0 (no disability) to 100 (maximum disability possible).

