### **10.6 Statistical method**

The primary efficacy analysis will follow the intention-to-treat (ITT) principle, including all randomly assigned patients. All analyses will be performed using R software, version 4.4.0 (R Foundation for Statistical Computing). Missing data for the longitudinal outcomes will be handled under the assumption of missing at random using multiple imputation. Imputation will be performed using the Multivariate Imputation by Chained Equations (MICE) package in R, generating 5 imputed datasets. The imputation model will include all longitudinal outcome measures from all-time points and all baseline covariates listed above. Results from the imputed datasets will be pooled according to Rubin's rules. Baseline characteristics will be summarized using descriptive statistics. For the continuous outcomes, between-group differences at each specific time point and within-group changes from baseline will be evaluated via pairwise comparisons of the estimated marginal means derived from the linear mixed model (LMM), which will be fitted using the lme4 package (version 1.1.35). These comparisons will be conducted using the emmeans package (version 1.10.0) with Tukey's method for adjustment of P values to control the

family-wise error rate. The model will include fixed effects for treatment group, time (modeled as a categorical factor), and their interaction. The model will be adjusted for the following prespecified baseline covariates: sex, age, body mass index, total duration of lumbar disc disease, duration of the current progressive episode, and degree of herniation at the symptomatic disc level. For categorical outcomes, between-group comparisons will be performed using the chi-square test or Fisher's exact test as appropriate, while the Bonferroni correction will be applied to adjust the significance level and control for type I error arising from multiple comparisons. All statistical tests will be two-sided, with a P value of less than .05 considered statistically significant. Institute of Basic Research in Clinical Medicine, China Academy of Chinese Medical Sciences will perform all statistical analyses.

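### The primary model omits baseline ODI and contrasts week-2 levels rather than change: this costs precision and mismatches the stated outcome, but does not bias the result

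*Protocol*

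**What the plan says.** Protocol Section 6.1, like the Endpoints row of the Summary, defines the outcome: "The primary outcome will be change in ODI from baseline to week 2".

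Section 10.6 fits a linear mixed model with group, categorical time and their interaction. For the covariates it says: "The model will be adjusted for the following prespecified baseline covariates: sex, age, body mass index, total duration of lumbar disc disease". The list ends with the duration of the current episode and the degree of herniation. That makes six covariates, and baseline ODI is not one of them. Of the contrasts it says that "between-group differences at each specific time point and within-group changes from baseline will be evaluated via pairwise comparisons of the estimated marginal means".

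Change from baseline thus appears only as a within-group quantity. Because it is obtained from the model's marginal means, baseline must be one of the time levels and the response must be the ODI score. No between-group contrast of change is stated, and no constraint that the arms share a baseline mean. ODI is measured on Day 0 (study schedule, Section 6.3). Apart from its place as a response at the first time level, baseline ODI is used only in the imputation model.

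**The concern.** The outcome is worded as a change, while the between-group test is worded as a difference at a time point. A reader of the results could take either the week-2 level difference or a difference in change as the primary answer, and the protocol does not say which.

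The second matter is efficiency. When group-by-time means are unconstrained, having baseline as a response lends nothing to the week-2 group contrast. If baseline ODI predicts week-2 ODI at all, the planned confidence interval is wider than the collected data allow. What is at stake is the width of the primary interval and the power of the two primary comparisons.

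**Working it through.** **Inputs.** From Section 3.2: a difference of 7 ODI points; an SD stated "with a standard deviation of 15.1 points derived from a pre-trial study", with no word on whether it is the SD of a score or of a change; "A statistical power of 90% and a two-sided alpha of 0.05 were assumed"; sizing "using the Dunnett's test for the two primary comparisons"; 15% dropout; final target 146 per group. From Section 10.6: the model, covariates and Tukey adjustment described above.

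**Assumed, because the documents do not give them.** The baseline to week-2 correlation r, taken from 0.3 to 0.7; equal SDs at baseline and week 2; a Tukey family of the three group comparisons at one visit.

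**Step 1: the plan's own figure.** "The initial calculation indicated a requirement of 113 participants per group". With the two-sided Dunnett critical value 2.221 (two comparisons, 336 df) and z = 1.282 for 90% power:

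n = 2 × (15.1 × (2.221 + 1.282) / 7)² = 114.2

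Exact power at 113 is 89.6%, so 113 is reproduced within rounding. Also 113 / 0.85 = 132.9, giving 133; 3 × 146 = 438; and 146 × 0.85 = 124 evaluable per arm.

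**Step 2: which contrast the planned model tests.** Data were simulated with 113 per arm, seven visits, a random intercept, r = 0.5, no covariates and no missing values. The model's week-2 group contrast equalled the raw difference in week-2 means to about 1e-13. Its mean SE was 2.01, against 1.74 with baseline ODI as a covariate. The formulas agree: 15.1 × √(2/113) = 2.009, and 2.009 × √0.75 = 1.740.

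**Step 3: variance relative to a comparison of levels.** Level: 1. Unadjusted change: 2(1 − r). Baseline-adjusted: 1 − r².

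| r | level | unadjusted change | adjusted |
|---|---|---|---|
| 0.3 | 1 | 1.4 | 0.91 |
| 0.5 | 1 | 1.0 | 0.75 |
| 0.7 | 1 | 0.6 | 0.51 |

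Unadjusted change beats levels only when r exceeds 0.5. Adjustment beats both for any r between 0 and 1.

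**Step 4: power per comparison at 124 per arm.** Power = Φ(7/SE − 2.353), where 2.353 is the Tukey critical value.

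- If 15.1 is the SD of the score, SE = 15.1 × √(2/124) = 1.918 for the planned contrast and 1.918 × √(1 − r²) with adjustment.
- If 15.1 is the SD of the change, the score SD is 15.1 / √(2(1 − r)), which is 12.76, 15.10, 16.88 or 19.49 at r = 0.3, 0.5, 0.6 or 0.7. The SEs follow in the same way.

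| r | SD of score: planned | SD of score: adjusted | SD of change: planned | SD of change: adjusted |
|---|---|---|---|---|
| 0.3 | 90.3% | 93.0% | 97.5% | 98.5% |
| 0.5 | 90.3% | 96.9% | 90.3% | 96.9% |
| 0.6 | 90.3% | 98.6% | 81.9% | 95.8% |
| 0.7 | 90.3% | 99.7% | 68.2% | 94.6% |

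At r = 0.5 the adjusted SE is 1.661. The unadjusted analysis would need 124 / 0.75 = 165 evaluable per arm to match it.

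**The case against.** The strongest reply is that nothing here is invalid. Under randomization the arms have the same expected baseline, so the difference in week-2 levels and the difference in change have the same expectation. If 15.1 is the SD of the score, the planned analysis reaches its 90% target at 124 per arm even with Tukey. All of that stands.

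Three further replies stand in full or in part:

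- **Levels against change.** A reader might infer that testing levels when the outcome is a change is itself what loses precision. It is not. At r = 0.5 the two are equal, and below 0.5 an unadjusted change score is worse. The loss comes from leaving out baseline adjustment.
- **Chance imbalance.** A reader might count chance baseline differences as an extra harm. With a baseline SD of 15.1 (assumed), a one-SE imbalance is 15.1 × √(2/146) = 1.77 points and shifts the unadjusted contrast by 0.5 × 1.77 = 0.88 points at r = 0.5. That variation is already inside the unadjusted standard error, so it adds nothing to the loss shown above.
- **What the plan already uses.** Baseline ODI informs imputed week-2 values, so the effective number lies between 124 and 146 per arm. At 146 the planned contrast has 94.6% power if 15.1 is the SD of the score. The six covariates may also explain part of what baseline ODI would explain. The gains shown are therefore upper bounds.

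One reply does not stand: that the matter belongs to a separate analysis plan. The protocol itself closes the covariate list, calls it prespecified and names the contrasts, so an analysis plan that added baseline ODI would depart from it.

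**Conclusion.** The point holds as a loss of precision and a mismatch in wording. It is a recommended improvement, not a defect that must be cured before the analysis can be trusted.

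If 15.1 is the SD of the score, the variance of the week-2 contrast could fall by up to r², that is 9% to 49% for r from 0.3 to 0.7. If it is the SD of the change, the planned contrast drops below the 90% target once r passes about 0.5, while the adjusted one stays near 95% or above throughout the range. Both statements rest on an assumed r, equal SDs at the two visits, 124 completers per arm and no credit for the listed covariates.

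A reader might go further and infer bias, an inflated type I error or a sample size that is too small. The documents do not support the first two, because randomization protects the level contrast. The third is not shown either: it would need 15.1 to be the SD of the change and r to be above about 0.5, and the protocol states neither.

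**What to change.** In Section 10.6, name the primary contrast as the between-group difference in change in ODI from baseline to week 2, and estimate it in one of two ways:

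- keep baseline as a response but give all arms a common baseline mean (constrained longitudinal model); or
- take baseline out of the response and add baseline ODI and its interaction with time as covariates.

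Treat leg pain VAS, low back pain VAS and SF-12 in the same way, each with its own baseline. An unadjusted change score is not the remedy, since it is less precise than the planned contrast when r is below 0.5. It would also help if Section 3.2 said whether 15.1 is the SD of the score or of the change.

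The cost is wording only. All these measures are already taken on Day 0, and no visit, patient or procedure is added. The change should be made before unblinding so that it counts as prespecified.

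### The primary comparison is sized on Dunnett's test for two contrasts (section 3.2) but analysed with Tukey's all-pairs adjustment (section 10.6): two decision rules for one endpoint, at a cost of about 2 points of power at the planned enrolment

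*Protocol*

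**What the plan says.** Protocol section 3.2 (Sample size) states the primary objective as "demonstrating the superiority of the combination therapy over YBT or LOPM alone" and bases the calculation on "detecting a MCID of 7 points on Oswestry Disability Index", "with a standard deviation of 15.1 points derived from a pre-trial study". It adds: "A statistical power of 90% and a two-sided alpha of 0.05 were assumed". The test is fixed too: "using the Dunnett's test for the two primary comparisons". The result follows: "The initial calculation indicated a requirement of 113 participants per group". This is raised to 133 for 15% dropout and then to 146 per group (438 in all), with multicentre recruitment given as the reason for the last step.

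Section 6.1 makes the change in ODI from baseline to week 2 the primary outcome.

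Section 10.6 (Statistical method) handles all continuous outcomes together. Differences between groups at each visit, and changes from baseline within groups, are taken as pairwise comparisons of marginal means from a linear mixed model, with "Tukey's method for adjustment of P values". The primary endpoint gets no rule of its own, and Dunnett's test is not mentioned in that section.

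**The concern.** The two sections name different multiplicity procedures for the same primary endpoint. Dunnett's test controls the family-wise error over two contrasts that share the combination arm. Tukey's method controls it over all three pairs and so sets aside some of the error for YBT against LOPM, which is outside the stated primary objective.

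Two things are at stake. The first is the decision rule: a primary contrast with |t| between 2.22 and 2.35 is significant under the rule in section 3.2 and not under the rule in section 10.6. If this is left open until the data are seen, the choice could be made with knowledge of the result. The second is power: the sample size was worked out for a less strict test than the one written into the analysis.

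**Working it through.** **Inputs (section 3.2, with 1:1:1 allocation from section 5.1).** Difference δ = 7 ODI points; SD σ = 15.1; two-sided α = 0.05; target power 90%; three equal groups of n; dropout 15%.

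**Formulas.**
- Noncentrality of one contrast: λ = δ / (σ·√(2/n)), with pooled error df = 3n − 3.
- Per-comparison power: P(|T| > c), where T is noncentral t with df and λ.
- Dunnett c: two-sided 5% point of the larger of two |t| statistics with correlation 0.5, by numerical integration.
- Tukey c: q(0.95; 3, df) / √2, where q is the studentized range.

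**The plan's own figures.** At n = 113, λ = 7 / (15.1 × √(2/113)) = 7 / 2.009 = 3.48 and Dunnett c = 2.221, so power is 89.6%. Exactly 90% needs 115. The stated 113 therefore reproduces, within two participants, as a per-comparison Dunnett figure. The dropout step also reproduces: 113 / 0.85 = 132.9, rounded up to 133.

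**The same contrast under Tukey.** At n = 113, c = 2.354 and power is 87.0%. Reaching 90% needs 124 evaluable per group, and 124 / 0.85 = 145.9, that is 146 enrolled.

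**At the planned enrolment.** 146 × 0.85 = 124.1, so about 124 evaluable, where λ = 7 / (15.1 × √(2/124)) = 7 / 1.918 = 3.65.

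| n per group | Dunnett c | Tukey c | Power, Dunnett | Power, Tukey |
|---|---|---|---|---|
| 113 (calculated) | 2.221 | 2.354 | 89.6% | 87.0% |
| 124 (146 less 15%) | 2.221 | 2.353 | 92.3% | 90.2% |
| 146 (no loss) | 2.219 | 2.352 | 95.9% | 94.6% |

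**The gap on the ODI scale.** At 124 per group with SD 15.1, the standard error of a difference is 1.918. The two thresholds are 2.221 × 1.918 = 4.26 points and 2.353 × 1.918 = 4.51 points. An observed difference between about 4.3 and 4.5 points would pass one rule and fail the other.

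**The case against.** The best defence is that the trial as enrolled loses nothing that it promised. The target in section 3.2 is 146, not 113, and after the plan's own 15% dropout the 124 who remain are just what Tukey needs for 90%. Tukey is also conservative for the two primary contrasts, so the mismatch works against the sponsor's claim and not for it. Guarding YBT against LOPM in a three-arm trial is a reasonable choice. All of this stands. It limits the consequence but does not remove the contradiction. The rise to 146 was made for recruitment, so it absorbs the penalty by coincidence, and the protocol still gives two thresholds for its primary test.

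A reader might go further and take section 10.6 as one Tukey family over all three groups and seven assessment times: 21 means and 210 pairs. The critical value would then be about 3.60, and per-comparison power roughly 46% at 113 and 52% at 124, treating the means as cross-sectional. The text does not describe that family. It asks for differences between groups at each visit (3 pairs × 7 visits = 21) and changes from baseline within groups (6 later visits × 3 arms = 18). That is 39 contrasts; the other 171 pairs are never requested. The wording points to three groups per visit. It is fair to say only that the boundary of the family could be drawn more clearly, particularly because within-group changes do not fit a family of three groups at one visit.

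**Conclusion.** The inconsistency is real and concerns the primary test: section 3.2 and section 10.6 prescribe different adjustments for the week-2 ODI contrasts. Its size is modest. Per-comparison power drops from 89.6% to 87.0% at the calculated 113 per group, and from 92.3% to 90.2% at the planned 124 evaluable.

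Two stronger conclusions might be inferred and are not supported. The enrolled trial is not underpowered against its own 90% target, and the type I error for the two primary contrasts is not inflated. The point is of moderate severity.

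The figures assume a Tukey family of three groups at one visit, the stated difference and SD, equal groups and 15% loss. Covariate adjustment in the mixed model and multiple imputation may change power, but the protocol gives no figures from which to say by how much. Power is per comparison, which is the basis on which 113 reproduces. Power to win both contrasts is lower under either test (86.9% Dunnett and 83.7% Tukey at 124).

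**What to change.** Settle this before unblinding, in one of two ways.

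1. **Preferred.** In section 10.6, define the primary family as two week-2 contrasts from the linear mixed model, combination against YBT and combination against LOPM, with Dunnett's adjustment as in section 3.2. Report YBT against LOPM, the other visits and the within-group changes as secondary, outside that family. The cost is a sentence and one changed contrast specification. The only loss is that YBT against LOPM has no claim within the primary family.
2. **Alternative.** Keep Tukey for the primary test, limit it explicitly to the three groups at week 2, and restate section 3.2 as 124 evaluable and 146 enrolled per group under Tukey. The cost is about 2 points of power compared with Dunnett at the same size.

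Neither route needs more participants or visits.

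### On the plain reading of Protocol 10.6, the six baseline covariates cancel from the arm difference in ODI change to week 2, so the stated adjustment does not act on the primary outcome as defined

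*Protocol*

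**What the plan says.** Protocol section 6.1 sets the endpoint: "The primary outcome will be change in ODI from baseline to week 2". The same section gives seven assessment times: "Efficacy measures will be recorded at baseline and 3 days, 1 week, 2 weeks, 6 weeks, 14 weeks, and 26 weeks after randomization".

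Section 10.6 sets the model: "The model will include fixed effects for treatment group, time (modeled as a categorical factor), and their interaction". It then says: "The model will be adjusted for the following prespecified baseline covariates: sex, age, body mass index, total duration of lumbar disc disease", and the list goes on to the duration of the current episode and the degree of herniation. Group-by-time is the only interaction named. Baseline ODI is not in the list.

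On contrasts, 10.6 says that "between-group differences at each specific time point and within-group changes from baseline will be evaluated via pairwise comparisons of the estimated marginal means". Since change from baseline is read off marginal means of this same model, baseline is one of the visits and the response is ODI itself, not a change score.

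On missing data: "Imputation will be performed using the Multivariate Imputation by Chained Equations (MICE) package in R, generating 5 imputed datasets". The covariates also enter that step: "The imputation model will include all longitudinal outcome measures from all-time points and all baseline covariates listed above".

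**The concern.** A covariate that is fixed over time and has one coefficient for all visits shifts a patient's expected ODI equally at baseline and at week 2. Subtract one from the other and it is gone. The protocol lists prognostic factors to adjust for and defines its primary outcome as a change, yet in the model as written those factors cannot influence the arm difference in that change. Readers would take the primary result as adjusted for episode duration, herniation degree and the rest. For the change contrast there would be no gain in precision, and no correction for chance imbalance in factors that affect how fast patients improve.

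**Working it through.** **Inputs from the Protocol.** Section 3.2: difference 7 points, SD 15.1, power 90%, two-sided alpha 0.05, Dunnett's test for two comparisons, 113 per group, 15% dropout, 133, then 146 per group. Section 6.1: seven visits. Section 10.6: model terms, covariates and imputation as above.

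**The plan's own figure.** The two-sided Dunnett critical value for two comparisons (correlation 0.5) is c = 2.212. Then n = 2 × [15.1 × (2.212 + 1.282) / 7]² = 113.6, which agrees with 113 within tolerance. Also 113 / 0.85 = 132.9, so 133, and 3 × 146 = 438. No covariate gain is built into this figure.

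**Algebra.** For patient i in arm g at visit t, the plain reading is E(Y_it) = μ_gt + x_i′β.

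- Change: E(Y_i,wk2 − Y_i,0) = μ_g,wk2 − μ_g,0. The term x_i′β has dropped out.
- Estimation: take complete data and one covariance matrix V for all patients. Generalised least squares splits each patient's data into a weighted mean m_i = 1′V⁻¹Y_i / (1′V⁻¹1) and within-patient contrasts c′Y_i with c′1 = 0. Their covariance is 1′c / (1′V⁻¹1) = 0. Only m_i carries β. Group-by-visit leaves the arm means of the contrasts unrestricted, so each is estimated by the raw arm mean.
- The point estimate therefore does not depend on the random-effects structure, which the Protocol does not state. Imputation makes each dataset complete, so the cancellation is exact.
- Level at week 2: adjusted difference = raw difference − (x̄_a − x̄_b)′β̂. Here β̂ comes from m_i, which under a random intercept is the plain average of all seven visits.

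**Numerical check.** One simulated complete dataset: 146 per arm, seven visits, six covariates with assumed effects on both level and change, random-intercept REML fits. Comparisons 1 and 2 are each single-treatment arm against the combination; SE in brackets.

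| Model | Change to week 2, comparison 1 | Change to week 2, comparison 2 | Week-2 level, comparison 1 |
|---|---|---|---|
| No covariates | 4.66730 (1.409) | 3.00688 (1.409) | 5.749 (1.690) |
| Six main effects | 4.66730 (1.409) | 3.00688 (1.409) | 4.362 (1.323) |
| Covariate-by-visit terms | 4.146 (1.344) | 3.303 (1.336) | 4.350 (1.294) |

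- The raw differences in mean change are 4.66730 and 3.00688, identical to the first two rows.
- Generalised least squares with an arbitrary common covariance gave 4.66730 in absolute value (SE 0.33633), with and without the covariates.
- With some visits deleted and no imputation, the cancellation was only approximate (5.273 without the covariates, 5.186 with them).
- The level contrast is adjusted: (1.323 / 1.690)² = 0.61, about 39% less variance here. By-visit terms would take that variance down by a further 4% or so: (1.294 / 1.323)² = 0.96.
- A week-2 ANCOVA of change on group and the six covariates gave 4.146 (SE 1.384) and 3.303 (SE 1.376), the same point estimates as the by-visit model. Change on group alone had SE 1.517. Adding baseline ODI gave 4.259 (SE 1.183) and 3.947 (SE 1.177).

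**Size.** The Protocol gives no R² for the covariates, so a range is assumed. The variance ratios come from 3,000 simulations with a single covariate (by-visit adjustment against main effect only). Power per comparison at n = 113 is Φ(7 / [15.1 × √(1 − R²) × √(2/113)] − 2.212), taking 15.1 as the SD of the change.

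| Assumed R² for week-2 change | Variance ratio | Variance saved | Equivalent extra patients (1/ratio − 1) | Power at 113 |
|---|---|---|---|---|
| 0% | 1 | 0% | 0% | 89.8% |
| 5% | 0.950 | 5% | 5% | 91.4% |
| 10% | 0.911 | 9% | 10% | 92.8% |
| 15% | 0.858 | 14% | 17% | 94.1% |

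**The case against.** The strongest reply is that the cancelling contrast is not one that section 10.6 names. It names the between-arm difference at each visit and the within-arm change, both as pairwise comparisons of marginal means. An arm difference in change is a difference of differences. On the named between-arm contrast the covariates do work. This stands, and it rules out saying that the covariates are idle throughout the plan. It does not rescue the primary outcome: the level difference at week 2 is not a test of change from baseline, and the Protocol does not say which contrast tests the endpoint in 6.1.

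Four further points limit the finding:

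- That the covariates enter as main effects only is inferred. Section 10.6 names one interaction and lists the covariates separately, but it does not exclude covariate-by-visit terms, and a SAP could add them.
- A reader might infer that all protection against chance imbalance is lost. It is not. Subtracting baseline already removes any constant covariate contribution, imbalance included. Only imbalance in factors that affect the trajectory goes uncorrected.
- A reader might infer bias or an undersized trial. Neither follows. Treatment is randomised, and section 3.2 claims no covariate gain.
- The shift from 4.667 to 4.146 is one simulated draw, about 0.4 of a standard error, and not an expected effect.

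Treating change scores as the response would stop the cancellation, but it fits poorly with 10.6, which obtains change from baseline by comparing marginal means. The covariates also enter the imputation model. That affects the imputed values, but not how the arms are contrasted once the data are complete.

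**Conclusion.** The point holds in a limited form. If ODI at all seven visits is the response, the covariates have one coefficient each, the covariance is common to all patients and outcomes are imputed to completeness, the six covariates have exactly no effect on the fitted arm difference in change to week 2. The adjustment in 10.6 then does not act on the outcome defined in 6.1. The contrast on which it does act is a level, adjusted by a coefficient pooled from baseline to week 26.

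The loss is efficiency: about 5% to 14% of variance if the covariates explain 5% to 15% of week-2 change. Those percentages are assumed, and with no explanatory power nothing is lost. The estimate stays unbiased and the 113 per group is unaffected. This is worth correcting because the covariates are already prespecified and the correction is small, not because the trial would otherwise be invalid.

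**What to change.** In Protocol section 10.6, name the arm difference in ODI change from baseline to week 2 as the contrast that tests the primary outcome. Estimate it in each imputed dataset by ANCOVA of week-2 change on group and the six listed covariates, and pool by Rubin's rules. Baseline ODI is already collected and can be added at no cost. The mixed model can stay for the other visits and outcomes.

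Alternatively, keep one model and add covariate-by-visit terms for the six covariates.

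The cost is one additional model in the first case. In the second it is about 6 covariates × 6 post-baseline visits = 36 parameters, more if degree of herniation has several levels; that is small for 438 patients with seven visits each. Neither option needs new data or a change in sample size.

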Therefore, focusing on LDHR patients with moderate pain, we will conduct a multicenter, randomized, three-arm parallel-group controlled trial to evaluate the efficacy and safety of combination of YBT and LOPM.

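### The Bonferroni rule for categorical outcomes in section 10.6 does not exempt adverse events, where it makes a true excess harder to detect

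*Protocol*

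**What the plan says.** The Background section of the protocol gives the trial's purpose as "to evaluate the efficacy and safety of combination of YBT and LOPM", although the formal objective in section 2 speaks only of therapeutic effect. Section 6.1 states: "Secondary outcomes will include leg and low back pain VAS, SF-12, adverse events, and disc resorption rates". Of the outcomes named there, adverse events and disc resorption are the two that are naturally categorical.

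Section 10.6 has one between-arm rule for categorical outcomes: a chi-square or Fisher's exact test, "while the Bonferroni correction will be applied to adjust the significance level and control for type I error arising from multiple comparisons". The rule does not name adverse events, exempt them, or say how many comparisons are counted. Tests are two-sided at .05 before correction.

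Section 10.3 defines the safety set as everyone randomized who received the assigned intervention at least once. It gives no separate comparison method. Sections 7.2 to 7.5 deal with grading, causality and documentation, not with comparing arms.

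**The concern.** The same correction has opposite merits for the two kinds of outcome it covers. For disc resorption the costly error is to claim a benefit that is not there, and Bonferroni protects against that. For adverse events the costly error is to overlook a real excess, and Bonferroni makes that more likely.

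This matters here because the combination arm is exposed to both the manipulation-related and the drug-related events listed in section 7.1. The comparison of the combination with each single treatment is therefore where an excess would be looked for. At stake is the sensitivity of the safety comparison; the ODI result is not affected. The point concerns a rule that the protocol states, not something it leaves to a statistical analysis plan.

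**Working it through.** **Inputs from the protocol (section 3.2).** "The calculation was based on detecting a MCID of 7 points on Oswestry Disability Index"; "with a standard deviation of 15.1 points derived from a pre-trial study". "A statistical power of 90% and a two-sided alpha of 0.05 were assumed". Multiplicity was handled "using the Dunnett's test for the two primary comparisons". "The initial calculation indicated a requirement of 113 participants per group". The target is 146 per group.

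**The plan's own figure.** The two-sided Dunnett critical value for two comparisons (correlation 0.5, large degrees of freedom) is 2.212, and the normal quantile for 90% power is 1.282.

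n = 2 × ((2.212 + 1.282) × 15.1 / 7)² = 113.6, against 113 stated. Power at 113 is 89.8%.

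113 / 0.85 = 132.9, so 133. 3 × 146 = 438.

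The stated sample size is reproduced. It is a calculation for ODI; the protocol states no power, rate or margin for adverse events.

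**Assumptions for adverse events.**
- Event rates: not stated; baseline rates of 2% to 20% are examined.
- Divisor: not stated. Three pairwise comparisons give .05 / 3 = .0167. Two comparisons, combination versus each single treatment, give .05 / 2 = .025.
- Arm size: 146. The safety set in section 10.3 keeps everyone treated at least once, so an arm size reduced for dropout is not the natural basis.

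**Method.** Exact enumeration of two binomial counts with n = 146 each. The test is the uncorrected chi-square when expected counts are at least 5, and Fisher's exact test otherwise. The miss rate is the probability that P is not below alpha when the rate truly doubles.

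| True rates | alpha .05 | alpha .025 | alpha .0167 |
|---|---|---|---|
| 2% v 4% | 89% | 94% | 95% |
| 5% v 10% | 64% | 74% | 79% |
| 10% v 20% | 32% | 43% | 50% |
| 15% v 30% | 13% | 20% | 24% |
| 20% v 40% | 3% | 6% | 8% |

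**Share due to the correction (three comparisons).** For 5% v 10%: 79 − 64 = 15 points. For 10% v 20%: 50 − 32 = 18 points. With two comparisons the additions are 74 − 64 = 10 and 43 − 32 = 11 points. At the ends of the range there is less to add: 95 − 89 = 6 points from a 2% baseline and 8 − 3 = 5 points from 20%.

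**Share due to sample size.** The alpha .05 column is the miss rate with no correction. By the normal approximation, 80% power at alpha .05 for a doubling would need 435 per arm (5% v 10%) or 199 per arm (10% v 20%), against 146.

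**What an interval would show.** The 95% half-width for equal rates of 5% is 1.96 × √(2 × .05 × .95 / 146) = 5.0 points, and for equal rates of 10% it is 6.9 points. Observed rates of 5% and 10% give a difference of 5 points (about −1.0 to 11.0). That interval includes zero but shows plainly how large an excess the data still allow.

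**The case against.** **Coverage is inferred.** Section 10.6 speaks of categorical outcomes and never names adverse events, which have their own analysis set and their own case-level assessment. That is so. But they are listed as a secondary outcome, no other between-arm method is given, and the literal reading places them under the rule.

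**Safety action does not wait for a corrected P value.** Termination for excess serious events (section 4.6), 24-hour reporting (5.6) and ethics committee review (11.2, 11.7) run independently of it. This stands, and it limits the consequence to the comparison reported at the end.

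**Missing intervals may be in the statistical analysis plan.** This also stands. The absence of a confidence interval from a protocol is not a finding, and nothing in section 10.6 forbids one. The finding is the blanket correction, from which an analysis plan would have to depart.

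**Stronger readings that the protocol does not support.**
- A reader might infer that a non-significant test will be reported as no difference in safety. The protocol nowhere says so; it is a risk to guard against.
- A reader might conclude that a doubling would be missed half to 80% of the time as a matter of fact. That range needs baseline rates of about 5% to 10% and a divisor of three, neither of which is stated.
- A reader might attribute the whole miss rate to Bonferroni. A trial sized for ODI would miss many of these excesses without any correction.
- A reader might measure the miss rates against a 20% ceiling. The protocol sets none for harms; its 90% power applies to ODI only.

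**Whether harm comparisons should be corrected is partly a matter of judgement.** Dropping the correction does produce more chance signals, which is a real cost.

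**Conclusion.** The point holds in a limited form. Section 10.6 applies a type I error correction to adverse events along with efficacy outcomes, and for harms that works in the wrong direction. The direction does not depend on any assumed rate; the size does. With 146 per arm, three comparisons and baseline rates of 5% to 10%, the correction adds about 15 to 18 points to the chance of missing a doubling; with two comparisons it adds about 10 to 11. Over baseline rates of 2% to 20%, the miss rate with three comparisons runs from 95% to 8%, so no single figure describes the trial. Because much of the miss rate remains when the correction is removed, a non-significant P value would be weak reassurance either way, and an interval is the better basis for the safety statement. It is a minor drafting defect, worth correcting because correction is cheap.

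**What to change.** In section 10.6, limit the Bonferroni correction to disc resorption and any other categorical efficacy outcome. For adverse events, report on the section 10.3 safety set the rate in each arm and the risk difference of the combination versus each single treatment, with unadjusted 95% confidence intervals. State that the safety conclusion will be based on those intervals and not on a non-significant P value.

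This takes one or two sentences and needs no new data or change of sample size. The price is a few more chance safety signals, which should be labelled exploratory. It does not give the trial adequate power for adverse events; it makes the remaining uncertainty visible.
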